## Abstract

**Background:**

Most surviving hip-fracture patients experience reduced mobility and lose some of their functional ability, which increases the risk of complications and rehospitalization. Post-discharge transitional programs to reduce readmissions and disabilities have shown some success. Telerehabilitation refers to the use of technologies to provide rehabilitation services to people in their homes. Considering the need for long-term follow-up care for people with hip fracture, in-home telerehabilitation could increase independence, decrease hospital stays and reduce the burden for caregivers. The objective of this study is to investigate the effectiveness of an intervention program based on telerehabilitation on activities of daily living (ADL), quality of life (QOL), depression and burden on caregivers compared to face-to-face home visits and usual care of community-dwelling older adults after hip fracture.

**Methods/design:**

This will be a three-armed randomized control trial (RCT) including pre/post intervention and follow-up. The trial will include 90 older people with hip fractures who will be randomly assigned to a telerehabilitation group (*N* = 30), face-to-face visits (N = 30) and a control group. The aim of the intervention is to improve the transition from rehabilitation units to community dwelling. It will include 10 videoconferencing/ face-to-face sessions from an occupational therapist in the presence of the primary caregiver. Each session will be utilized to guide the participants to achieve their self-identified goals, focusing on problem-solving for daily life situations and on the ability to implement the discussed strategies for a variety of activities. Outcome measures include Functional Independence Measure (FIM) for evaluation of ADL, SF-12 for evaluation of Health-related QOL, The Geriatric Depression Scale (GDS) and The Zarit Caregiver Burden Scale. Data will be analyzed using Repeated measures MANOVA.

**Discussion:**

The current study will enable the cost-effectiveness examination of a suggested rehabilitation service based on available technology. The proposed intervention will increase accessibility of in-home rehabilitation services, improve function and health, and reduce economic burden.

**Trial registration:**

NCT03376750 (12/15/2017).

## Background

Hip fracture is one of the most serious osteoporotic fracture, and the second most common cause of hospitalization among the age group older than 65 years [1]. Hip fractures occur predominantly in the geriatric population [2, 3], due to higher rates of osteoporosis and falls [4]. The lifetime risk of hip fracture is 9% for women and 4% for men [5]. Hip fractures are a major public health problem in terms of patient morbidity, mortality and costs to health and social care [4, 6]. With an ageing population, and a growing proportion of people aged 80 years or older, the societal and economic burden of osteoporosis-related fractures is deemed to be increasing [7]. The healthcare costs for hip fractures are the highest (€20,000/patient) in comparison with other costs of injuries [8]. Osteoporotic hip fractures incur a high economic cost mainly due to the first hospitalization [8], but also due to subsequent outpatient visits, home care [6] and complications following initial hospital discharge [4, 9]. Therefore, further research is needed to identify the most effective and cost-effective rehabilitation pathways for these patients [10].

A third of older adults with hip fracture will be readmitted to hospital within 30 days of their return home [11], and up to 20% of patients die in the first year following hip fracture [12]. Hip fractures have profound effects on quality of life (QoL) and activities of daily living (ADL) [13, 14]. Most patients surviving hip fracture experience reduced mobility, lose their functional ability [15] and independence [16], and suffer from depression [17]. A systematic review found that after 1 year, 29% of hip-fracture patients did not reach their pre-fracture level of ADL, and 35% were not able to walk independently [2].

Hip fractures nearly always necessitate hospitalization and rehabilitation [18, 19]. Rehabilitation is a significant factor impacting the level of functional independence following hip fracture [20]. In the United States, more than 90% of Medicare beneficiaries utilize post-acute-care rehabilitation after an acute hip fracture hospitalization [21]. In Israel, 73.5% of the hip-fracture patients received inpatient rehabilitation, 14.3% received ambulatory rehabilitation treatment without an inpatient phase, and 12.2% received no rehabilitation [22].

The objective of rehabilitation is successful community discharge— facilitating a safe return to the community, thereby minimizing the likelihood of long-term institutionalization or reentry into the healthcare system [21]. However, a substantial decline in functional ability of hip-fracture patients occurs 1 year post discharge from rehabilitation. More than half of the hip-fractured elderly patients were unable to maintain their rehabilitation achievements 1 year post discharge [23]. Thus, to be efficacious in reducing or reversing disability after hip fracture, rehabilitation needs to be individualized, include many components, be progressive, and span a sufficiently long period [24].

Transitions between healthcare settings are a high-risk period for care quality and patient safety, mainly for older patients – such as those with hip fracture – who have complex needs and may undergo multiple care transitions [25]. Particularly for older adults, transitions are often plagued with discontinuity and a lack of coordination [26]. Patterns and problems associated with transitions after hip fracture in older adults include weight loss, delirium, depression, pressure ulcers, falls, and urinary incontinence [27], resulting in increased use of hospital, ambulatory and emergency services [26]. Gaps in communication and timely delivery of information are commonly cited barriers for inter-professional teams working along the continuum of care [25]. Strategies to improve transitional care to older hip-fracture patients should include improved patient and family involvement at the time of transition [27], communication and information sharing [25].

To summarize, hip fractures are one of the most common and potentially devastating injuries amongst the geriatric population [1]. The incidence, morbidity, and medical costs associated with hip fracture among the elderly are well-recognized [20]. The economic burden associated with hip fractures calls for the investigation of innovative and cost-effective forms of services [28]. Healthcare providers should be aware of the necessity for an individualized, holistic, long-term post-rehabilitation intervention program to prevent functional decline [9, 23].

Traditional in-home therapy provides the opportunity for rehabilitation intervention to occur within the context of everyday task performance [29]. Moreover, home rehabilitation programs have positive long-term effects in comparison with conventional care after hip fracture in elderly people [30–33]. Nonetheless, although in-home rehabilitation has been generally successful in preventing ADL decline [34] and facilitating recovery of ADL functioning and locomotion [35], problems caused by distance, the cost of travel and absence of healthcare personnel limit its utility [36]. To overcome these limitations, several studies have demonstrated that in-home therapy delivered to the elderly using interactive video-conferencing can successfully treat ADL task-performance deficits [37–39]. These studies suggest that relatively inexpensive video-conferencing technology can maintain the patient-therapist interactions, and provide a pragmatic alternative to face-to- face home visits by a therapist for improving function [36] and reducing healthcare spending [39].

This “telerehabilitation” strategy for chronic and prolonged disease management involves the patient in the process of medical care, provides continuous medical monitoring and early symptoms detection allows the ability to promptly respond to an acute exacerbation [40]. In addition, it can help to lower the psychological threshold for accessing medical care in people who are not aware of the seriousness of their symptoms, or who might otherwise be reluctant to access face-to-face care [41]. The evolving telecommunications industry has been proposed as a realistic solution to reduce healthcare cost, time, hospital visits [42] and caregiver burden [43], and provide long-term and easily accessible remote medical services [39, 44]. By using telerehabilitation services, client access to care can be improved and the reach of clinicians expanded, thus enhancing the continuity of care to persons with disabling conditions [45, 46]. A study that compared the effectiveness of video-conferencing with traditional outpatient clinic visits in the implementation of the management plan showed that video-conferencing is a valid alternative for orthopedic specialist consultations [47]. The results of another study suggest that conducting pre-admission occupational therapy “home visits” via the Internet with patients who are scheduled to undergo a total hip or knee replacement is both feasible and accurate [48].

Recent studies demonstrated the potential of home-based telerehabilitation in older adults and individuals with mobility impairment [49, 50]. As far as we know, however, only one paper so far has aimed to assess the impact of an older patient’s acceptance of hip-fracture telerehabilitation. They found that this intervention protocol targeting individualized impairments was feasible, safe and effective for use in home-based rehabilitation of older adults after hip fracture [51]. However, this research included only 10 patients and employed a quasi-experimental pre/post design without control group or follow-up. A study with longer duration and larger sample size, which also includes follow-up, needs to be done to measure hip-fracture recovery outcomes including functional parameters.

Some papers have addressed the issue of cost-effectiveness of telerehabilitation services to older adults. The first research assessed the feasibility of providing home-based telerehabilitation as an alternative to traditional ambulatory rehabilitation in patients post stroke, fracture or long hospital admission. There was a 50% reduction in staff’s home visits due to the telerehabilitation intervention. The therapists were able to provide twice the amount of service and direct patient-contact time, whilst reducing by 50 % time they spent travelling [52]. In addition, the effectiveness of a virtual reality-based telerehabilitation program for balance recovery after stroke was compared with conventional physical therapy program in the clinic. Results showed that the clinic-based intervention had a higher cost relative to the virtual reality intervention [53]. An Israeli case study described novel integrated motor imagery treatment designed for the rehabilitation of walking, which was delivered in the home through telerehabilitation for a person after stroke. Compared with on-site delivery, the telerehabilitation sessions resulted in lower therapist travel time and cost, as well as shorter therapy sessions [54]. Economic analyses were conducted as part of trials using telerehabilitation for total knee arthroplasty [55, 56]. The cost for a single session of in-home telerehabilitation compared to conventional home-visit rehabilitation was lower or about the same, depending on the distance between the patient’s home and healthcare center. A favorable cost differential was observed when the patient was more than 30 km from the provider [56]. Even if transportation costs were excluded, telerehabilitation was still a cost-effective alternative to usual care [55].

To summarize, the idea of telerehabilitation is becoming a more concrete means to deliver services to patients in their home environment, allowing patients to gain self-confidence in their ability to manage their health conditions [46]. Recent studies demonstrated the potential of home-based telerehabilitation in older adults [47, 49, 50] and its cost-effectiveness [52, 53]. However, limited evidence exists on the feasibility of home-based telerehabilitation in older adults after hip fracture**.**

## Methods

### Study aims

The primary aim of this study is to compare the effectiveness of in-home telerehabilitation and face-to-face home visit intervention programs, as opposed to the standard care currently offered to community-dwelling older adults after hip fracture. The secondary aims of this study are: (1) to evaluate the maintenance of the interventions’ accomplishments 3 months after completion; (2) to estimate the cost-effectiveness of the intervention programs; and (3) to understand the user experience of the patients and caregivers.

### Trial design, randomization and recruitment

This study is a three-armed, evaluator-blind, randomized control trial (RCT) and will be implemented according to CONSORT guidelines [57]. Participants will be assigned to research and control groups by using a blocked randomized controlled design, stratified based on age. The randomization sequence will be computer generated and will be known only to the responsible investigator.

All participants will be recruited at the time of discharge from hospital. Health professionals employed at the hospital will screen and refer to a research assistant the interested clients who meet the inclusion criteria. The research assistant will obtain informed consent from caregivers and patients prior to randomization and trial inclusion. Participants (*n* = 90) will be randomized after baseline assessment in the three-arm study. The rehabilitation program will be identical in both intervention groups; only the delivery mode will differ: in-home telerehabilitation or face-to-face home visit. The patients allocated to all groups will continue to receive the standard usual care to improve adherence to intervention protocols. All outcomes will be measured at all three time points: Baseline-pretest (T0), immediately following intervention (post intervention 10 weeks) (T1), and a 6-month follow-up (T2) (See Fig. 1).

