**Fig. 1 Fig1:**
[figure not shown]
Schematic illustration of the study design

Recruitment and baseline testing will be carried out at Herzog and Hadassah Medical Centers, Jerusalem Israel. Intervention sessions will be conducted by video-conferencing or face-to-face visit while the participants are at their homes. Post-intervention and follow-up assessments will be carried out by e-mail or phone. The participation in the study will discontinue upon participants’ request.

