#### Inclusion criteria

Older adults (age ≥ 60 years) after hip fracture, who will be discharged from the rehabilitation or orthopedics units of Herzog and Hadassah Hospitals, Jerusalem, between January 2017 and December 2019. Discharge will be from rehabilitation to a non-institutionalized setting. Patients with broadband or Wi-Fi in their home and able to operate an iPad or computer independently. Functional Independence Measure [49] score at rehabilitation discharge: FIM > 90. Every participant will designate a caregiver (a close friend, family member, or support worker) aged over 18, who will agree to cooperate in the research and be present during the interventional phases to promote participants’ retention.

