### Control group

The purpose of the control group is to control for changes that may occur with the passage of time in the estimate of the efficacy of the intervention [70]. This group will receive the usual care and rehabilitation by the common routine for patients with hip fracture, and will be discharged with no further therapy as part of the study. In addition, the clinicians will receive no direction from the research study staff.

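### Two hospitals recruit but randomisation is stratified by age only; adding hospital to the list or the model is a cheap gain in balance and precision

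*Protocol article*

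**What the plan says.** The protocol article, under Trial design, randomization and recruitment, gives the allocation scheme: "Participants will be assigned to research and control groups by using a blocked randomized controlled design, stratified based on age". Age is the only factor named. The same section says that health professionals employed at the hospital screen and refer eligible patients, and that randomisation of the 90 participants follows the baseline assessment.

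The text with Fig. 1 says "Recruitment and baseline testing will be carried out at Herzog and Hadassah Medical Centers, Jerusalem Israel". The inclusion criteria describe patients "who will be discharged from the rehabilitation or orthopedics units of Herzog and Hadassah Hospitals, Jerusalem", and the next sentence adds "Discharge will be from rehabilitation to a non-institutionalized setting".

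On usual care, the Control group section says "This group will receive the usual care and rehabilitation by the common routine for patients with hip fracture" and that "the clinicians will receive no direction from the research study staff". The trial design section adds that "The patients allocated to all groups will continue to receive the standard usual care".

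Data analysis describes a repeated-measures MANOVA with group, time and their interaction. No hospital or unit term is named.

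**The concern.** Hospital is a natural candidate for a prognostic factor here. Each hospital's staff decide whom to refer, so case mix may depend on the hospital. Usual care runs in all three arms and the study does not standardise it, so recovery after discharge may depend on the hospital too. An age-stratified list does nothing deliberate to spread hospitals evenly over the arms, and at 30 per arm chance alone can leave one arm with noticeably more patients from one hospital. If the hospitals then differ in change from baseline, that realised contrast is shifted. A model without a hospital term also leaves the between-hospital variation in the error.

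**Working it through.** The article gives no figure for hospital balance, so there is none to reproduce. Its sample size (25 per group, recruited as 30) enters only through the arm size. The 25 matches a two-sided calculation with d = 0.8, while the stated one-sided test gives 20 by the normal approximation. That is a separate matter, and nothing below depends on it.

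**Inputs from the article:** 90 participants in three arms of 30; 20% drop-out, leaving 30 × 0.8 = 24 per arm; planned d = 0.8.

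**Assumptions (not in the article):** the larger hospital supplies 50% to 80% of the 90; the hospitals differ by 0.3 to 0.8 within-hospital SD in change from baseline.

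**Step 1: chance imbalance.** The 90 were allocated at random to 30/30/30 without regard to hospital, 50,000 times per split. A 20-point gap is 6 patients out of 30.

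| Larger hospital's share | Gap ≥ 20 points, two given arms | Gap ≥ 20 points, any pair of the three | Gap ≥ 30 points, any pair |
|---|---|---|---|
| 50% | 15.6% | 32% | 7% |
| 60% | 15.0% | 31% | 6% |
| 70% | 12.2% | 26% | 4% |
| 80% | 7.8% | 17% | 1.5% |

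Check by formula: the SD of the gap between two arms is √[2p(1−p)(90/89)/30]. This gives 0.130 at p = 0.5 and 0.104 at p = 0.8; the simulation gave 0.129 and 0.104. The mean signed gap is zero. The simulation treats hospital as unrelated to age and to order of entry. If it is related, blocking within age would remove part of the imbalance.

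**Step 2: effect on a contrast.** Shift = gap × hospital difference in change.
- 0.20 × 0.3 = 0.06 SD
- 0.20 × 0.5 = 0.10 SD
- 0.20 × 0.8 = 0.16 SD

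The standard error of a two-arm difference at 24 per arm is √(2/24) = 0.29 SD. The shift is therefore 0.06/0.29 = 0.21 to 0.16/0.29 = 0.55 of a standard error.

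**Step 3: precision from a hospital term.** With difference δ and share p, the variance without the term is 1 + p(1−p)δ² relative to within-hospital variance, so the standard error falls by 1 − 1/√[1 + p(1−p)δ²].
- p = 0.5, δ = 0.3: 1 − 1/√1.0225 = 1.1%
- p = 0.5, δ = 0.5: 1 − 1/√1.0625 = 3.0%
- p = 0.5, δ = 0.8: 1 − 1/√1.16 = 7.2%
- p = 0.8, δ = 0.3: 1 − 1/√1.0144 = 0.7%

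**The case against.** The strongest case on the other side is that stratifying by age alone is a legitimate choice in a small trial, that nothing in the text is wrong or contradictory on this point, and that separate lists per hospital or a hospital covariate may stand in a full protocol or analysis plan that is not shown. Both hospitals are in one city, and common entry rules (FIM above 90, the MOCA cut-off, discharge to a non-institutional setting) narrow the case mix. An unstratified test already allows for chance imbalance. Because baseline is in the repeated-measures model, a constant difference in level between hospitals, including one produced by inpatient rehabilitation before T0, cancels from change. Only a difference in change matters, and 0.5 SD or more of that is a strong assumption.

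Most of this stands, and it limits the point to a minor one. It does not remove the point. The article states its stratification factor rather than leaving it open, and hospital is not it. Baseline adjustment also cannot absorb differences in care after discharge.

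A reader might infer more: that each hospital has its own usual-care routine, or that the two recruit from different unit types. The documents do not support either. The Control group section speaks of a single common routine; the absence of study direction permits variation but does not document it. The inclusion criteria list units and hospitals jointly and assign no unit type to either hospital. Their following sentence, on discharge from rehabilitation, sits badly with the mention of orthopedics units. Those two sentences need reconciling, but they are not evidence of a hospital difference.

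**Conclusion.** The point holds as a minor improvement. Age is the only stratification factor named, two hospitals feed arms of 30, and the described model has no hospital term. A gap of 20 points or more between two given arms has a chance of about 8% to 16% over the assumed splits. It would move that contrast by 0.06 to 0.16 SD over the assumed hospital differences in change. A hospital term would take about 1% to 7% off the standard error. The shift is small beside the planned d = 0.8. That effect size, however, comes from face-to-face home rehabilitation against conventional care, and the article states none for telerehabilitation against face-to-face visits, where the same shift could weigh more.

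It would be wrong to read this as bias or confounding by hospital. Imbalance under randomisation is centred on zero, the estimates stay unbiased and the tests stay valid. It would also be wrong to conclude that hospital is left uncontrolled in the final analysis, since an adjustment could be set out in a document not shown. Both the recruitment split and the hospital difference are assumptions.

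**What to change.** Generate the allocation list within hospital as well as age, with small blocks in multiples of three, and name hospital and age as factors in the analysis. With two age bands (the article does not give the number) this makes 2 × 2 = 4 strata. If recruitment has already started, leave the list alone, prespecify a hospital term in the analysis and report allocation by hospital and arm.

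The sample size does not change. The cost is regenerating a computer list, a few more incomplete blocks at the end of recruitment, and one degree of freedom for hospital.

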**Fig. 1 Fig1:**
[figure not shown]
Schematic illustration of the study design

Recruitment and baseline testing will be carried out at Herzog and Hadassah Medical Centers, Jerusalem Israel. Intervention sessions will be conducted by video-conferencing or face-to-face visit while the participants are at their homes. Post-intervention and follow-up assessments will be carried out by e-mail or phone. The participation in the study will discontinue upon participants’ request.

